**Outcome measures/variables:**

Primary outcome measure will be time to resolution of severe pneumonia.

Secondary outcome measures will be duration of hospitalization, fever, tachypnoea, chest in drawing, hypoxia, lethargy and inability to feed during hospital stay and as well as new episode of pneumonia after discharge.

## Data Analysis

Data will be entered onto a personal computer (PC) and analysed by the principal investigator using STATA. We will perform the Chi-square test to compare categorical variables, and unpaired t test or ANOVA (Analysis of Variance) to compare quantitative variables. Intention to Treat (ITT) analyses will be done for assessing the impact of vitamin D supplementation on the outcome variable. To compare the median duration of each outcome variables Kaplan-Meier survival function plots will be done. To adjust the treatment effects for potential confounding factors and to evaluate the effect modification Cox proportional hazard regression model will be done. P value will be considered as significant when less than 0.05. Risk ratio (RR) will be estimated to compare the recovery rate in the two groups. Incidence rates of pneumonia will be calculated by dividing the number of new episodes of pneumonia by total time at risk for all children. Hazard ratios with 95% CIs will be obtained with Cox proportional-hazards models to measure time to repeat episodes between treatment groups.

## Data Safety Monitoring Plan (DSMP)

Data will be accessible to the PI, co-investigators, study physician and members of IRB. All the activities in this study will be closely monitored by PI and Co PIs. However a data safety and monitoring board (DSMB) will be there to meet at regular intervals for the monitoring of safety issue on vitamin D toxicity and any serious adverse event will be reported to the board.

## Ethical Assurance for Protection of Human rights

The study protocol and data collection tools, and the informed consent forms to be used in the study will be submitted to the Ethical Review Committee (ERC) of icddr,b, and the study would be initiated only after receiving approval of the committee. All medical information, description of treatment, and results of the laboratory tests performed will be kept under lock and key, only research staff, hospital physicians and nurses, and ERC/DSMB members of icddr,b will have access to these information.

## In this study we will see the impact of vitamin D on severe pneumonia among under five children. Although researchers first identified the fat-soluble vitamin D (cholecalciferol) almost a century ago, we know a little about mechanisms of vitamin D toxicity. Even with current data support the viewpoint that the biomarker plasma 25(OH)D concentration must rise above 750 nmol/L to produce vitamin D toxicity, the more prudent upper limit of 250 nmol/L might be retained to ensure a wide safety margin. Therefore for this study to ensure the safe dose of vitamin D3 for the children we will first proceed through piloting. We will observe any adverse event after the intervention and monitor the serum 25(OH)D level on admission, at discharge (day 5) and after two weeks of discharge as the half life of vitamin D3 is two weeks. We will also do serum calcium level on day of admission, 2nd day and at discharge for safety monitoring as vitamin Ds primary roll is to control the levels of calcium in the body by constantly adding calcium to or taking calcium from bones. Depending on the findings of this pilot phase, we will decide the final dose for vitamin D3 intervention for the study. We will consider the toxic level of 25(OH)D as 250nmol/L33,34 and the upper limit of the serum calcium would be 2.63 mmol/L for safety monitoring.35 If we find serum 25(OH)D and calcium level on admission above this level we will stop further intervention.

For the main phase of the study we will do serum test for ionized calcium instead of total calcium.

As we have considered the upper normal limit of total serum calcium for safety monitoring, in case of ionized calcium the upper limit (normal range: 1.15-1.33 mmol/L) will be considered for safety monitoring. So the child having ionized calcium above 1.33mmol/L on admission will be stopped from having further intervention and excluded from the study.

## Use of Animals

The study will not involve the use of any animal.

## Collaborative Arrangements

Not applicable.

## Facilities Available

The study will be conducted at the Dhaka Hospital of the International Centre for Diarrhoeal Disease Research, Bangladesh (icddr,b), Dhaka, Bangladesh. This hospital has separate ward for management of children with severe pneumonia, well equipped laboratory facilities capable of performing all the clinical tests and serological measurements proposed in this study and also has an Intensive Care Unit, equipped with mechanical ventilation and other facilities of management of critically ill patients, as well as properly trained clinical staff to provide care to young patients suffering with severe pneumonia.

**ANNEXURE**

**ANNEXURE-2: CASE REPORT FORM (CRF)**

**Vitamin D supplementation: Impact on severe pneumonia among under-five children**

Child’s name: ………………………………………………………………………………………………

Father’s name: ……………………………………………………………………………………………..

Address: ……………………………………………………………………………………………………..

…………………………………………………………………………………………………….

Phone number: ………………………………………………………………………………………………

**Socio-demographic History:**  **Code**

1. Study ID number
2. Date of admission

3. Date of enrolment

4. Date of discharge

5. Hospital Registration No:

6. Allocation number

7. Allocation group:1=A, 2=B

# 8. Place of normal residence of the patient

(1=within Dhaka city, 2=within Dhaka district, 3= outside Dhaka district)

9. Age (in months)

10. Sex: 1=Male , 2= Female

11. Religion of the patient

(1= Muslim, 2=Hindu, 3=Christian, 4=Buddhist, 5= Others)

12. Gestational age at birth (weeks) [ code 99, if not known)

13. Father’s age (in years)

14. Mother’s age (in years)

15. Education of Patient’s Father

(1=none, 2=maktab, 3=1-5 yrs of schooling, 4=6-10 yrs, 5=10-12 yrs, 6= >12 yrs of schooling)

16. Education of Patient’s Mother

(0=none, 1=maktab, 2=1-5 yrs of schooling

3=6-10 yrs, 4=10-12 yrs, 5= >12 yrs of schooling)

17. Father’s occupation

(1=unemployed, 2= day labourer, 3=hawker, 4=petty business

5= garments worker, 6=private job, 7= govt.job, 8=driver, 9=rickshawpuller)

18. Mother’s occupation

(1=house wife, 2= garments worker, 3= day labourer,

4= private job, 5= govt. job, 6= maid servant, 7=street begger)

19. Family History of Tuberculosis

(1=yes, 2=no)

20. Family History of respiratory tract infection (within past 14days) (1=yes, 2=no)

21. Past History of pneumonia

(1=no pneumonia, 2=1 time, 3=2 times, 4=>2 times)

22. Breast feeding

(1=yes, 2=no, 9=not applicable)

23. Duration of breast feeding (in months)

24. Exclusive breast feeding

(1=yes, 2=no, 9=not applicable)

25. If non breast fed then type of feed

(1=cereal, 2=formula milk, 3=cow’s milk, 4=others)

26. Duration of complementary feeding (in months)

27. Number of rooms in the house hold

28. Number of adults sharing the same sleeping area with the child

29. Number of children sharing the same sleeping area with the child

30. Cooks inside bedroom

(1=yes, 2=no)

31. Monthly income (BDT)

32. History of smoking in the family

(1=none smokes, 2=father smokes, 3=mother smokes, 4=both parents smoke

5= other family member smokes)

33. Type of locality where care giver live?

(1=slum, 2=common housing area, 3= residential area, 4= village, 5= others)

34. Dwelling status (sun exposure)

(1=not at all, 2=mild, 3=moderate, 4=adequate)

35. How much time spends at outdoor daily (in hours)?

36. Percentage of body covered with clothes when outdoor (%)

[according to “rule of nines”- head and neck (18%), body (36%),

upper limb (18%), lower limb (28%), genitalia (1%)]

37. Number of siblings

38. Birth order of the diseased child

39. Number of under-five children in the family other than the diseased child

40. How many people live in the family?

41.Immunization status

BCG 1= Yes, 2=No , 3=Don’t know, 9=NA

Penta 1 1= Yes, 2=No, 3=Don’t know, 9=NA

Penta 2 1= Yes, 2=No, 3=Don’t know , 9=NA

Penta 3 1= Yes, 2=No, 3=Don’t know, 9=NA

Oral polio 4 1=Yes, 2=No, 3=Don’t know, 9=NA

MR 1= Yes, 2=No, 3=Don’t know, 9=NA

Measles 2 1=Yes, 2=No, 3=Don’t know, 9=NA

42. Whom did you consulted first for this episode of illness of your child?

(1= qualified doctor, 2= homeopath doctor 3= spiritual adviser

4= quack, 5= drug seller, 6=traditional healer, 7= others, 8=none)

43. Why delay (if any)?

(1= financial constraint, 2= to take care at home, 3= under treatment of quack

4= under homoeopath or spiritual treatment, 5= could not realise the problem

6= single at home, 7= others, 9=not applicable)

44. a. Use of antibiotics before admission in hospital

(1=yes, 2=no, 3=don’t know, 4=not applicable)

b. Name of antibiotic used before admission in hospital

(1=Amoxycillin, 2=Cefixime, 3=Azythromycin, 4=Ciprofloxacin, 5=Ceftriaxone

6=Cefpodoxime, 9=Don’t know)

45**. Symptoms on admission**

| **Symptoms** | **1 = yes / 2 = no** | **Duration in days** |
| --- | --- | --- |
| Diarrhoea  (Type of diarrhea:1=AWD,2=ID,3=PD) |  |  |
| Cough |  |  |
| Running nose |  |  |
| Fever |  |  |
| Vomiting |  |  |
| Respiratory distress |  |  |
| Poor oral intake |  |  |
| Lethargy |  |  |
| Convulsion |  |  |
| Others 1 |  |  |
| Others 2 |  |  |
| Others 3 |  |  |
| Others 4 |  |  |

46.**Clinical Examination**

**A) ANTHROPOMETRY**

- Admission height/length (cm)
- Admission weight (kg)
- W/A%
- ZW (z score)
- W/L%
- WL (z score)

- L/A%
- LA (z score)

**B) General examination**

- Radial pulse (rate/min) [ If imperceptible, code “000”]
- Respiratory rate (per minute)
- Axillary temperature (°C)
- Pallor

(1=yes, 2=no)

- Cyanosis

(1=yes, 2=no)

- Icterus

(1=yes, 2=no)

- Clubbing

(1=yes, 2=no)

- Pedal edema

(1=yes, 2=no)

- Lymphadenopathy

(1=yes, 2=no)

- Spo2 (%)
- Dehydration

(1=no sign, 2=some, 3=severe, 9=not applicable)

**C) Systemic examination**

1. **Respiratory system**

- Lower chest wall in drawing 1=yes, 2=no
- Nasal flaring 1=yes, 2=no

- Central cyanosis 1=yes, 2=no
- Grunting 1=yes, 2=no
- Head nodding 1=yes, 2=no
- Crackles 1=yes, 2=no
- Rhonchi 1=yes, 2=no
- Bronchial breathing 1=yes, 2=no
- Wheezing 1=yes, 2=no

1. **Cardiovascular system**

- Murmur

(1=yes, 2=no)

c**) Abdominal system**

- Liver palpable

(1=yes, 2=no)

- Spleen palpable

(1=yes, 2=no)

**d) Central nervous system**

Glasgow coma scale(GCS)

Physician’s initials: ____________ Date: ___/___/_____

47**. Laboratory investigations**

- Total WBC/cu.mm (Not done= 99)
- Poly% (Not done= 99)
- Lymphocytes (%) (Not done= 99)
- Immature poly (Band) % (Not done= 99)
- Hct% (Not done= 99)
- Sodium; mmol/L (Not done= 99)
- Potassium; mmol/L (Not done= 99)
- Chloride; mmol/L (Not done= 99)
- TCO2; mmol/L (Not done= 99)
- HCO3; mmol/L (Not done= 99)

- C-reactive protein on admission (Not done= 99)
- Blood glucose on admission(mmol/L) (Not done= 99)
- Serum “25 (OH)-D”level on admission(nmol/L) (Not done= 99)
- Serum “25 (OH)-D”level on discharge(nmol/L) (Not done= 99)
- Serum ionized Ca on admission(mmol/L) (Not done= 99)
- Serum ionized Ca on discharge(mmol/L) (Not done= 99)
- Serum phosphorus on admission(mmol/L) (Not done= 99)
- Serum Alkaline phosphatase on admission(U/L) (Not done= 99)
- Serum PTH on admission (pmol/L) (Not done= 99)
- Serum PTH at discharge (pmol/L) (Not done= 99)
- Blood culture 1=Positive, 2= Negative, 3=Not done

- Blood culture isolate :

(1=Streptococcus pneumoniae, 2=Staphylococcus aureus, 3=Haemophylus influenzae, 4=Salmonella typhi, 5=Salmonella para-typhi, 6=Non typhoidal Salmonella, 7=E. Coli, 8=Klebsiella, 9=Enterococcus, 10=Acinetobacter, 11=Pseudomonas,12=CNS, 13=Enterobacter species , 14=Poly microbial)

- Chest X-ray findings:

(1=normal, 2=primary end point consolidation, 3=other consolidation/infiltrate,

4=pleural effusion, 5=pneumothorax)

48**. Diet with Vitamin D3:/ Diet without Vitamin D3:**

| Day | Date | Time | Dose given | If any vomiting within 30 mins, repeat the dose | If any adverse effect* |
| --- | --- | --- | --- | --- | --- |
| 1. |  |  |  |  |  |
| 2. |  |  |  |  |  |
| 3. |  |  |  |  |  |
| 4. |  |  |  |  |  |
| 5. |  |  |  |  |  |

(*Adverse effect: vomiting, decreased appetite, irritability, constipation, dehydration, fatigue, muscle weakness)

49. **Antibiotics given:**

| Antibiotics | 1=yes,2=no | Day started | Day stopped | Comments |
| --- | --- | --- | --- | --- |
| Ampicilin |  |  |  |  |
| Gentamicin |  |  |  |  |
| Ceftriaxone |  |  |  |  |
| Levofloxacin |  |  |  |  |
| Ceftazidime |  |  |  |  |
| Amikacin |  |  |  |  |
| Flucloxacillin |  |  |  |  |
| Vancomycin |  |  |  |  |
| Imipenem |  |  |  |  |
| Meropenem |  |  |  |  |
| Cotrimoxazole |  |  |  |  |
| Ciprofloxacin |  |  |  |  |
| Clarithromycin |  |  |  |  |

50. The amount of vitamin D received through dietary source (IU)

(Infant formula/milk siji)

51. Final Outcome

- - - 1. Well & discharged
      2. Did not improve but discharged on request
      3. Died in hospital

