**Secondary objectives:**

- To compare the duration of hospitalization, fever, tachypnoea, chest in drawing, hypoxia, lethargy and inability to feed during hospital stay, in under-five children in the two study groups, as mentioned under the primary aim.
- To compare the recurrence of new episode of pneumonia over the next 6 months after discharge from hospital in the two study groups.
- To identify the optimum safety dose of vitamin D3 for different groups of under-five children.
- In severe pneumonia patient who also have acute watery diarrhoea we will assess the indirect absorption of vitamin D by measuring serum vitamin D level and will also assess the clinical outcome in the subgroup.

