A hospital-based, randomised, controlled trial in Kabul shows that supplementation of a bolus dose of 100,000 IU vitamin D in addition to antibiotic to young children with pneumonia was associated with reduced repeat episode of pneumonia, without reducing the hospital stay.26 Another study in India reported no beneficial effect of small consecutive dose of vitamin D with antibiotics on resolution of severe pneumonia among under five children.27

However limited information is available in Bangladesh about the vitamin D status in children. A survey conducted at Dhaka neighborhood found that among 319 children between the age group of 16 to 20 months and 164 children between the age group of 30-36 months respectively 51% and 43% had blood vitamin D (25-OH-D) level below the cut off value (47.7 nmol/L) of 25-OH-D (Personal communication from [name], unpublished). From the data on National Rickets Survey in Bangladesh in 2008, it was documented that 98% children were vitamin D deficient out of 154 rachitic children (Personal communication from Dr. [name], unpublished) and a study from Chakaria observed that 2 (20%) children out of 10 rachitic children were vitamin D deficient.28 A matched case-control study in North-Eastern part of Bangladesh noted a relationship between Vitamin D status and early childhood ALRI, and young age group was the only risk factor for vitamin D deficiency.29

Although many studies have shown the association between vitamin D deficiency and pneumonia, there is limited information on the effect of vitamin D supplementation in the outcome of children with pneumonia.12, 19-27 We are, therefore, interested to conduct a randomised, controlled clinical trial to assess the impact of vitamin D supplementation, in addition to standard antibiotic therapy, on the duration of hospitalization, as well as on the duration of severe pneumonia of the affected children and further new episode of pneumonia.

Moreover co-morbidity of pneumonia and diarrhea is a burning public health problems accounting more than one third of 7.6 million global childhoods under five deaths30,31 and evaluation of the role of vitamin D in such population may have great value.

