For piloting we will enroll 20 patients and group them into two that is ten patients in each group. We will intervene one group with vitamin D3 supplement 10,000 IU for five consecutive days. Another group will receive stratified dose of vitamin D3 according to age. That is 20,000IU vitamin D3 in children <6 months, 50,000 IU in children 6-12 months and 100,000 IU in children 13-59 months of age on first day and thereafter 10,000 IU for next 4 days. We will observe any adverse event after the intervention and monitor the serum 25(OH)D level on admission, at discharge (day 5) and after two weeks of discharge as the half life of vitamin D3 is two weeks. To collect blood sample after two weeks of discharge parent/guardian will be requested for follow up visit at hospital with the child at that time. In case of failure to visit the hospital study staff will visit their home for follow up of the child and collection of blood sample for serum 25(OH)D level assay. We will also monitor serum calcium level on day of admission, 2nd day and at discharge for safety monitoring as vitamin Ds primary roll is to control the levels of calcium in the body by constantly adding calcium to or taking calcium from bones. Depending on the adverse event and serum 25 (OH)D and calcium level of this pilot phase, we will decide the final dose for vitamin D3 intervention for the study. We will consider the toxic level of 25(OH)D as 250nmol/L33,34 and the upper limit of the serum calcium would be 2.63 mmol/L for safety monitoring.35 If we find serum 25(OH)D and calcium level on admission above this level we will stop further intervention. After finalization of dose in this study we will assay the 25(OH)D and calcium level on admission and on 5th day or earlier at discharge.

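### CRF item 47 codes a laboratory test not done as 99, which is a possible real result for 25(OH)D, chloride, C-reactive protein and alkaline phosphatase (minor)

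*Protocol*

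**What the plan says.** The laboratory section of the case report form (Protocol annexure, CRF item 47) lists 20 numeric results, and each carries 99 as its code for a test not done. The unit and plausible range of the test make no difference. Examples:

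- chloride: "Chloride; mmol/L (Not done= 99"
- serum 25(OH)D, first sample: "level on admission(nmol/L) (Not done= 99"
- serum 25(OH)D, last hospital sample: "level on discharge(nmol/L) (Not done= 99"
- C-reactive protein, printed without a unit: "C-reactive protein on admission (Not done= 99"
- alkaline phosphatase: "Serum Alkaline phosphatase on admission(U/L) (Not done= 99"

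Blood culture, in the same list, has its own category for a test not done (code 3), so the form separates the two states there.

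25(OH)D has a stated use. Under Secondary objectives, for children who also have acute watery diarrhoea, the protocol says "we will assess the indirect absorption of vitamin D by measuring serum vitamin D level". It also gives two reference marks for this measurement. The Background reports children with a "level below the cut off value (47.7 nmol/L) of 25-OH-D", and the Study Intervention section says "We will consider the toxic level of 25(OH)D as 250nmol/L".

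**The concern.** A missing-value code has to be a value that the measurement cannot take. The code 99 meets that test for ionized calcium, whose normal range is given as 1.15-1.33 mmol/L. It does not meet it for 25(OH)D in nmol/L. It also fails, on general knowledge, for chloride in mmol/L, C-reactive protein and alkaline phosphatase in U/L. In those fields one number stands for two different states. A range check would not flag it, and a later analysis plan cannot restore a distinction that was never recorded.

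The two possible handlings do different harm. Setting every 99 to missing discards genuine results of 99. Leaving 99 in the data enters untested children as if measured and pulls every group mean towards 99. What is at stake is the 25(OH)D absorption objective and the descriptive laboratory tables.

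**Working it through.** The plan states no figure to reproduce here, since the point concerns a recording rule. The check asks whether 99 lies inside the possible range, and what each handling would cost.

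**1. Is 99 a possible result?**

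- 25(OH)D: 47.7 < 99 < 250 nmol/L, using the protocol's own marks. Yes.
- Ionized calcium: normal range 1.15-1.33 mmol/L. No, so the code is unambiguous there.
- Chloride, C-reactive protein, alkaline phosphatase: the protocol gives no ranges. Taking 99 as possible is an assumption from general knowledge.

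**2. Loss if 99 is set to missing.** Assume normal distributions and results recorded as whole numbers. With mean m, standard deviation s and Φ the normal distribution function,

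P(result reads 99) = Φ((99.5 − m)/s) − Φ((98.5 − m)/s).

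All values of m and s below are assumptions, except that 47.7 is used as the admission mean for 25(OH)D because 51% and 43% of the surveyed children lay below it, so it is near the centre. Counts are scaled to 155 per group (310 in all), the largest row of the sample-size table; the protocol does not say which row was chosen.

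| Test | m | s | P(reads 99) | Expected count |
| --- | --- | --- | --- | --- |
| Chloride | 100 | 4 | 9.6% | 29.9 of 310 |
| Chloride | 102 | 5 | 6.7% | 20.6 of 310 |
| Chloride | 105 | 7 | 4.0% | 12.2 of 310 |
| 25(OH)D, admission | 47.7 | 20 | 0.07% | 0.2 of 310 |
| 25(OH)D, admission | 47.7 | 30 | 0.31% | 1.0 of 310 |
| 25(OH)D, discharge | 80 | 30 | 1.1% | 1.7 of 155 |
| 25(OH)D, discharge | 100 | 30 | 1.3% | 2.1 of 155 |
| 25(OH)D, discharge | 150 | 50 | 0.5% | 0.7 of 155 |

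**3. Distortion if 99 is left in.** With a fraction f not done, the recorded mean is (1 − f)·m + f·99. With the same f in both arms, the term f·99 cancels in the difference:

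recorded difference = (1 − f)·(m₁ − m₂).

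The difference therefore shrinks by the fraction f, whatever the true means. Example with f = 0.10 and assumed true means of 47.7 and 150:

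- low group: 0.9 × 47.7 + 0.1 × 99 = 52.8
- high group: 0.9 × 150 + 0.1 × 99 = 144.9
- difference: 92.1 instead of 102.3, a loss of 10%

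If f differs between arms, 99·(f₁ − f₂) no longer cancels and the bias can go either way.

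**4. After the fix.** With a code that no test can return, the overlap is zero for every item.

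**The case against.** The best answer is that the code is printed on the form, so an analyst who follows the form sets 99 to missing and loses almost nothing that matters. PTH makes this likely: it is sampled in every fifth patient only (Collection of Baseline Information), so about four in five PTH fields will hold the code by design and the 99s will have to be stripped before any laboratory summary. If 25(OH)D is entered to one decimal, as the 47.7 mark suggests it might be, exact collisions fall about tenfold. The answer boxes are not visible in the available text, so this cannot be judged. The site is a single hospital with its own laboratory, and the form carries the hospital registration number, so doubtful values can be looked up. All of this stands, and it limits the size of the point. It does not make 99 a sound code.

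A reader might infer more than the document supports:

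- *Either handling seriously corrupts 25(OH)D.* Setting 99 to missing costs about 1% of values or less.
- *The treatment difference in 25(OH)D would fall by 30%.* With assumed means of 50 and 120 and 30% missing, the recorded means are 0.7 × 50 + 0.3 × 99 = 64.7 and 0.7 × 120 + 0.3 × 99 = 113.7, so 70 becomes 49. But 30% is the dropout allowance in the sample-size section, not a rate of missed hospital blood samples. The result also needs the printed code to be ignored.
- *Untested children would pass the safety rules.* The laboratory-based exclusion and stopping rules of the main phase rest on calcium, measured as ionized calcium, where 99 cannot be a result. The 250 nmol/L mark belongs to the pilot-phase text.
- *The effect-modification analysis is compromised.* The Data Analysis section names no 25(OH)D modifier.
- *The loss of chloride values matters to the trial's conclusions.* No objective, outcome or named analysis uses chloride, C-reactive protein or alkaline phosphatase.

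**Conclusion.** The point holds and is minor. Item 47 uses one code for all 20 numeric tests, and for four kinds of test that code is a possible result. For 25(OH)D this follows from the protocol's own marks; for the other three it rests on general knowledge of their ranges.

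Handled as the form directs, the cost is about 1% or less of 25(OH)D values and roughly 4-10% of chloride values, under assumed normal distributions and whole-number entry. If any 99 stays in, the 25(OH)D difference between arms shrinks by the fraction not done, assuming equal fractions. The reach is the 25(OH)D absorption objective and the laboratory descriptions. Time to resolution of severe pneumonia and the secondary outcomes listed under Outcome measures do not use these fields.

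**What to change.** In CRF item 47, replace 99 with a code outside the possible range of every test, or add a done/not-done box to each item and leave the result blank when the test was not done. A negative code such as -9 works for all 20 items. A large positive code such as 9999 would work for the others but not for total WBC per cu.mm, where it could be a real count.

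For forms already completed, check every 99 entered for 25(OH)D, chloride, C-reactive protein and alkaline phosphatase against the laboratory records and recode it as a result or as not done.

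The cost is one change to the form and the database code list, plus a one-off check of existing entries. No procedure, sample size or clinical rule changes.

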**Protocol Title:** Vitamin D supplementation: Impact on severe pneumonia among under-five children

| Project Summary |
| --- |
| Principal Investigator: [name] |
| Research Protocol Title: Vitamin D supplementation: Impact on severe pneumonia among under-five children |
| **Background:**   1. Burden: Pneumonia is the leading cause of morbidity and mortality in under-five children, particularly in developing countries. 2. Knowledge gap: Although many studies have reported an association between vitamin D deficiency and pneumonia, there is lack in information on its therapeutic impact, i.e. the impact of vitamin D supplementation in the management of childhood pneumonia. 3. Relevance: Vitamin D plays an important role in modulating the innate immune response against infections. We, therefore, propose to conduct this study to assess the impact of vitamin D supplementation, in addition to standard antibiotic and supportive therapy, on the outcome of severe childhood pneumonia.   **Hypothesis**: We hypothesise that in the management of hospitalized severe pneumonia in under-five children, vitamin D3 supplementation, as an adjunct to the standard antibiotic and other supportive therapy, will hasten recover from severe pneumonia and may thereby shorten duration of severe pneumonia and also reduce the risk of new episode of pneumonia.  **Objectives:** The objective of our study is to assess the clinical benefit of oral supplementation of vitamin D3, in addition to standard antibiotic and other supportive therapy, to hospitalised, under-five children with severe pneumonia.  **Methods:** This would be a randomised, double blind, controlled clinical trial (RCT). Children of either sex, aged 3-59 months, attending the Dhaka Hospital of icddr,b, with clinically diagnosed severe pneumonia will comprise the study population. Eligible children will be allotted a sequential study number, which will have been previously assigned to vitamin D or placebo in accordance with the randomisation. The study staff and mothers/ caregivers of the children will be blinded as to whether vitamin D3 or placebo has been added to their child's diet. Infants aged 3-5 months will receive breast milk and/or infant formula, and those 6 months or older will receive “Milk Suji” as a complementary food. Vitamin D3 supplementation will be given on five consecutive days, from the day of enrolment in addition to standard antibiotic and other supportive therapy.  **Outcome measures/variables:**  Primary outcome measure will be time to resolution of severe pneumonia.  Secondary outcome measures will be duration of hospitalization, fever, tachypnoea, chest in drawing, hypoxia, lethargy and inability to feed during hospital stay and as well as new episode of pneumonia after discharge. |

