**Randomisation and Allocation Concealment**

The eligible children will be allotted a sequential study number, which will have been previously assigned to vitamin D3 or placebo in accordance with the randomisation. A computer generated random list will be developed by a person not involved in the study in any way. Participants and the research staff will be blinded to allocation. Pharmaceuticals Company will prepare the supplements off-site using individual opaque glass vials labeled with concealed unique identifiers for vitamin D3 and placebo. Allocation concealment will be done by sealed envelope and will be kept in a secured place by the person not associated with the study in any way; the envelope will be opened at the end of the study only, prior to data analysis.

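### The case report form does not match the promised staff blinding: a dose log headed with both arms, a group letter shared by the whole arm, and an unmasked discharge 25(OH)D value

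*Protocol*

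**What the plan says.** **Blinding.** The Project Summary says that study staff and caregivers "will be blinded as to whether vitamin D3 or placebo has been added to their child's diet". The section Randomisation and Allocation Concealment says "Participants and the research staff will be blinded to allocation", describes "individual opaque glass vials labeled with concealed unique identifiers for vitamin D3 and placebo", and adds that "the envelope will be opened at the end of the study only, prior to data analysis".

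**The CRF.**
- Item 6 is an allocation number. Item 7, directly below it, is "Allocation group:1=A, 2=B".
- Item 48, the five-day log of date, time, dose, vomiting and adverse effects, is headed "Diet with Vitamin D3:/ Diet without Vitamin D3".
- Item 47 (Laboratory investigations) has an entry for serum 25(OH)D "level on discharge(nmol/L") and one for PTH at discharge.
- The same CRF holds the 8-hourly pneumonia status, which gives the primary outcome, and the 24-week pneumonia follow-up.

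**Access.** The Data Safety Monitoring Plan opens the data to the principal investigator, the co-investigators and the study physician. The Ethical Assurance section opens laboratory results to research staff and to the hospital's doctors and nurses. Neither section makes an exception for post-dose 25(OH)D or for the group letter.

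**The concern.** Much of the primary outcome is bedside judgement: under Monitoring during hospital stay, resolution requires the absence of signs such as chest in-drawing, lethargy and inability to feed. New pneumonia after discharge is elicited by telephone. Such outcomes are open to detection bias if the person judging them knows or suspects the arm.

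Unique vial identifiers protect against this, because learning one child's arm says nothing about the next child. A two-letter code removes that protection: once one letter is understood, every child whose letter is recorded is unblinded. Post-dose 25(OH)D is the natural means of working the letter out, and it is entered on the same form. Blinding lost in this way cannot be restored at analysis.

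**Working it through.** **1. Form against promise.**
- *Item 48.* Staff who do not know the arm cannot choose between the two headings. Either the heading is never completed, or someone who knows the arm completes it.
- *Item 7.* With unique vial identifiers and a sealed list, staff have no stated source for a letter during the trial. The form does not say who fills the item or when. Item 6 already identifies the allocation.
- *Item 47.* Nothing masks the discharge 25(OH)D, and both access statements include staff who treat or assess the children.

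**2. How easily could the letters be decoded?** The documents give no 25(OH)D response, so the standardised difference between arms, d, is an assumption shown over a range. The chance that one child's value classifies that child correctly is Φ(d/2). The chance that n values per letter rank A and B correctly is Φ(d·√(n/2)).

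| d (assumed) | one child | 5 values per letter |
|---|---|---|
| 0.5 | 0.60 | 0.79 |
| 1 | 0.69 | 0.94 |
| 2 | 0.84 | 0.999 |
| 3 | 0.93 | >0.999 |

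One value alone is a moderate clue unless d is large. A handful of values combined with a shared letter is a strong one.

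**3. Does the sample come before the primary outcome?** The documents give two timings.
- Collection of Baseline Information and the CRF place the sample at discharge. Criteria for Discharge require resolution of pneumonia, which includes at least 24 hours without fever or tachypnoea, so for a child discharged well the sample normally follows resolution of severe pneumonia.
- Study Intervention places it on day 5, or at discharge if earlier. With the sample-size section's control mean of 6 days and SD of 2.5, and a normal approximation, the share of controls unresolved on day 5 is 1 − Φ((5 − 6)/2.5) = 1 − Φ(−0.4) = 0.66. With a mean of 5 in the vitamin D group it is 0.50.

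Assay turnaround is not given, so even a day-5 sample may be reported after resolution.

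**4. What could a biased judgement do?** No shift is stated anywhere, so this is an illustration. One 8-hourly check is 8/24 = 0.33 day. At 108 per group, SE = 2.5·√(2/108) = 0.340. The false-positive rate of a two-sided 5% test under an average shift δ is Φ(−1.96 + δ/SE) + Φ(−1.96 − δ/SE).

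| children in one arm affected by one check | δ (days) | δ/SE | false-positive rate |
|---|---|---|---|
| none | 0 | 0 | 5.0% |
| a quarter | 0.083 | 0.245 | 5.7% |
| half | 0.167 | 0.49 | 7.8% |
| all | 0.333 | 0.98 | 16.5% |

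**The case against.** A reader might infer that the form prints each child's arm. It does not. Item 48 is a blank heading that names both alternatives. The two oils are described as identical in appearance and tasteless, and were tried in all three diets, so staff have nothing from which to choose.

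Nor does item 7 say which letter is vitamin D. It could be filled after the envelope is opened, in which case it does no harm. The decoding route needs three things that the protocol does not state: letters known during the trial, assay results returned in time, and someone who links the two.

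A child's own value mostly arrives at or after the end of that child's primary-outcome assessment. The outcome is also not wholly soft, because hypoxia is a pulse-oximeter reading with a numeric cut-off, which limits how far judgement can move the time of resolution. The Follow up section does not say that the health workers who telephone see the laboratory page.

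All of this stands, and it limits the point to a risk that the form leaves open. It does not remove the conflict: the form asks blinded staff for information they should not have, and the access statements withhold neither the letter nor the marker.

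**Conclusion.** The CRF and the access statements are inconsistent with the promised staff blinding. No single item reveals an arm. Taken together, they leave two routes:
- If the letter is entered during the trial, a few post-dose values could decode it for all children, and so reach the primary outcome in children enrolled later.
- A child's own value could inform those judging that child's later outcomes: late resolution, hospital stay, and new pneumonia over 6 months.

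The bias cannot be sized from the documents. The range of about 6% to 16.5% at 108 per group assumes a differential shift of 0.08 to 0.33 day. The upper end needs every child in one arm to be affected, which means complete unblinding from the start, and it should not be read as an expected rate. A similar calculation at 155 per group would give a higher figure, but 155 is enrolment inflated for 30% dropout, not the planned analysed number. A reader might also infer that staff did learn the allocation. The documents show only that the form and the access rules allow it.

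**What to change.** - **Item 7:** delete it. The allocation number in item 6 is enough.
- **Item 48:** retitle it *Study supplement* and record the identifier of the vial used.
- **Item 47:** remove post-baseline 25(OH)D and discharge PTH from the CRF seen by treating, assessing and follow-up staff. Hold them in a laboratory file until database lock. Admission values can stay.
- **Safety review:** route the withheld values through the DSMB already planned in the Data Safety Monitoring Plan. A rule that returns only out-of-range values to the ward would itself hint at the active arm, so the routing should be agreed with the DSMB. The main-phase stopping triggers that the protocol states use calcium, which this change leaves alone. How to act on any value remains for the clinical and safety team.
- **Consistency:** align the access statements in the Data Safety Monitoring Plan and the Ethical Assurance section, and the safety-monitoring text, with this. Reconcile the two timings given for the post-dose sample.

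The cost is a few reprinted CRF items, rerouted laboratory reports, and the DSMB's time to review the withheld values. No extra tests or visits are needed.
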